## 6 Procedures of the study

- (1) Patients meeting the enrolment criteria were included in this study after signing the informed consent form.
- (2) Patients were treated in strict accordance with the methods of this study.
- (3) Observe and follow up the patients during and after the treatment according to the methods of side effects and efficacy evaluation of this study.
- (4) To write a paper based on the data obtained from the study.

## **7 Trial Management**

The informed consent process involves a thorough explanation of the trial's objectives, procedures, and potential risks/benefits by the principal investigator. Participants must sign an Informed Consent Form (ICF), which includes both informational and signature pages. This process must comply with ethical standards, including the Declaration of Helsinki and CFDA's Good Clinical Practice (GCP) guidelines. Any protocol modifications require prior approval from the ethics committee. The original ICF is securely archived at the research site, while participants receive a copy for their records.

## **8 The risks and benefits**

- 8.1 The safety profile of this study is excellent and the risk to enrolled patients is low. The main side effects and adverse reactions that may occur during the study include: nausea, vomiting, fatigue, nausea, diarrhoea, abdominal pain, and leukocyte/platelet reduction. Phase I/II clinical studies have confirmed that the SOX regimen combined with simultaneous radiotherapy has a low incidence of both 3rd/4th degree toxicities and side effects, with nausea and leukopenia being the highest incidence; no life-threatening serious adverse effects occurred.
- 8.2 The benefit of this study is that it can explore the value of the SOX regimen combined with simultaneous radiotherapy after D2 radical surgery for gastric cancer, as well as its efficacy and safety, and find a more effective and safer treatment option for postoperative gastric cancer patients.

## **9 Adverse Events**

- 9.1 Definition of AE  
An Adverse Event (AE) refers to any undesirable medical occurrence in a study participant that coincides with the administration of an investigational drug, regardless of its causal relationship. This encompasses any unfavorable or unintended symptoms, signs, or medical conditions, whether treatment-related or not, including laboratory abnormalities necessitating clinical intervention (e.g., dose adjustment or treatment discontinuation). AEs are recorded from the moment informed consent is obtained until the completion of the protocol-defined follow-up period.

A Serious Adverse Event (SAE) is an AE that meets at least one of the following criteria: results in death, poses an immediate life-threatening risk, necessitates hospitalization or extends an existing hospital stay, leads to significant or persistent

disability/incapacity, involves a congenital anomaly or birth defect, or is deemed a medically critical event requiring intervention to prevent these outcomes. All SAEs must be reported within 24 hours of awareness, irrespective of causality. Investigators are responsible for assessing the potential relationship between the intervention and the event, ensuring thorough documentation and follow-up until resolution or stabilization.

## 9.2 Assessment of AE

All toxicity evaluations are evaluated based on the Common Terminology Criteria for Adverse Events (CTCAE) v4.0, published by the U.S. National Cancer Institute (NCI). The CTCAE v4.0 provides standardized grading criteria for AEs, categorizing their severity from Grade 1 to Grade 5, defined as follows: Grade 1 = mild, Grade 2 = moderate, Grade 3 = severe, Grade 4 = life-threatening, and Grade 5 = death. Radiotherapy-related adverse events are assessed using the Radiation Therapy Oncology Group (RTOG) Acute Radiation Morbidity Scoring Criteria from the initiation of treatment until 28 days post-radiation. Evaluations are conducted weekly during therapy and biweekly during follow-up, incorporating clinician-reported outcomes and patient-reported symptom diaries. The primary assessment domains include: dermatologic toxicity, mucosal injury, gastrointestinal toxicity, pulmonary complications.

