# 10 Study assessment

10.1 Effective evaluation indicators: The primary purpose is: DFS. The secondary purpose is: and OS.

10.2 Safety evaluation index: including all toxic side effects and adverse events observed during the trial.

10.3 Sample content estimation: we hypothesised that synchronous radiotherapy would result in higher DFS. with a double significance level of 0.05 and a certainty of 80%. We expect that the 3-year DFS of SOX regimen combined with simultaneous radiotherapy can be at least 8% higher than that of the chemotherapy-only group, i.e., from 70% to 78%. Based on the sample size formula for the comparison of the two sample rates, the sample size needed for this project was calculated to be 516 patients; assuming that 20% of the patients would need to be excluded from the statistics, the total number of patients that would need to be enrolled in this project would be 620.

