### **III. Radiotherapy Planning**

1. 3D-CRT, IMRT should be used;
2. Based on the CTV, the PTV should be expanded by 0.8 cm in the anterior, posterior, left, and right directions, and by 1.0 cm in the cranial-caudal direction;
3. Minimum dose covering 95% of the PTV: 50.4 Gy in 28 fractions; hotspot dose  $\leq$  107% of the prescription dose, with hotspot volume  $\leq$  2 cc;
4. Conformity index (CI)  $\geq$  0.8;
5. Dose constraints for major organs at risk: spinal cord  $\leq$  40 Gy, liver V30  $\leq$  33%, the dose to 33% of the volume of one kidney (most commonly the right kidney)  $<$ 15 Gy, mean dose to both kidneys  $<$ 15 Gy; small bowel D50  $<$ 20-30 Gy.

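### The AE definition leaves out radiotherapy and conflicts with its own recording window, and radiotherapy-specific scoring is acute only, so late radiation effects can be recorded but are not systematically sought or graded

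*Protocol*

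**What the plan says.** **Definition (Protocol, 9.1).** An adverse event is an undesirable occurrence that "coincides with the administration of an investigational drug, regardless of its causal relationship". Radiotherapy is not mentioned. A serious adverse event is defined as an adverse event meeting a further criterion, so it inherits the same limit.

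**Recording window (Protocol, 9.1, same paragraph).** "AEs are recorded from the moment informed consent is obtained until the completion of the protocol-defined follow-up period". Events count whether or not they are treatment-related. For serious events the investigator is responsible for "assessing the potential relationship between the intervention and the event", which is wider than a drug.

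**Grading (Protocol, 9.2).** The section opens with a general rule without a time limit: "All toxicity evaluations are evaluated based on the Common Terminology Criteria for Adverse Events (CTCAE) v4.0". It then assigns radiotherapy-related events to the "Radiation Therapy Oncology Group (RTOG) Acute Radiation Morbidity Scoring Criteria", applied "from the initiation of treatment until 28 days post-radiation". Evaluations are weekly on therapy and biweekly in follow-up, with no stated end. The named main domains are skin, mucosa, gastrointestinal tract and lung.

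**Safety index (Protocol, 10.2).** It is broad, "including all toxic side effects and adverse events observed during the trial".

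**Long-term visits (Protocol, 4.5).** Evaluations take place at least every 6 months in the first year and at least every 6-12 months after treatment. They consist of physical examination, imaging and laboratory tests including biochemistry. Toxicity grading is not listed.

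**Planning limits (Protocol, 4.4 and Appendix 2, part III).** Dose limits are set for spinal cord, liver, small bowel and kidney, the last including the "mean dose to both kidneys".

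**The concern.** The trial asks what radiotherapy adds after D2 surgery. It judges efficacy over 3 years, makes adverse events a secondary objective (section 3), and says in 8.2 that it hopes to find an option that is safer as well as more effective. A safety comparison on that horizon needs rules that clearly cover late effects of radiation.

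Here the definition does not name the tested modality, and the one instrument designed for it stops four weeks after the last fraction. Beyond that point a site has a general grading scale and a general duty to record, but no instruction to look for late radiation effects and no visit at which to grade them. In an open-label multicentre trial, sites can settle these gaps differently. Events not sought during follow-up cannot be recovered at analysis, so a later analysis document cannot repair this.

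**Working it through.** The protocol gives no late-toxicity rate and no safety calculation, so there is no figure to reproduce. The check is a comparison of the rules and a calendar built from the protocol's schedule.

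**1. Definition against recording window.** Assume no delays, six 21-day cycles in SOX, and day counts from the start of induction (taken as close to randomisation).

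- Radiotherapy starts at day 21 (4.2).
- 28 fractions at 5 per week (4.4) take 5 weeks plus 3 days: 5 × 7 + 3 = 38 days. Radiotherapy ends at about day 21 + 38 = 59.
- Post-radiotherapy SOX starts 3-4 weeks later: day 59 + 21 = 80 to 59 + 28 = 87.
- The last S-1 dose in SOXRT falls two cycles and 14 days later: 80 + 42 + 14 = 136 to 87 + 42 + 14 = 143.
- The last S-1 dose in SOX: 5 × 21 + 14 = day 119.

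Read strictly, coincidence with drug administration ends by about day 143 in SOXRT and day 119 in SOX. The recording window starts at consent, before any drug, and runs through follow-up, after all drug. The two sentences cannot both be applied literally.

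**2. Reach of the radiotherapy-specific assessment.** The RTOG window closes at 59 + 28 = day 87. Against 3 years (1,096 days) that is 87 / 1,096 = 7.9%. If treatment initiation means the start of radiotherapy, the window is 38 + 28 = 66 days, or 66 / 1,096 = 6.0%. From day 87 the remainder is 1,096 − 87 = 1,009 days, about 33 months, in which radiotherapy effects come under the general CTCAE and adverse-event rules alone.

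**3. Visit schedules.** The biweekly sentence directly follows the RTOG sentence. It may belong to that assessment, and so end with it, or govern all toxicity follow-up. If it ran from the last SOXRT dose to 3 years, reading biweekly as every 14 days, it would mean (1,096 − 143) / 14 ≈ 68 assessments. Section 4.5 implies a minimum of 2 evaluations in year 1 and 2 to 4 in years 2-3, so 4 to 6 in all. The protocol does not say when the first schedule yields to the second.

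**4. Organs.** The planning limits cover kidney, liver, spinal cord and small bowel. The 9.2 domains reach the bowel through gastrointestinal toxicity but name neither kidney, liver nor spinal cord. That list is not exhaustive, so this is a gap in emphasis and not a contradiction.

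**5. Length of follow-up.** The recording window ends with the protocol-defined follow-up period, but no section states how long that is. The 3-year endpoints imply at least 3 years.

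**The case against.** The strongest defence is that the general rules already cover late harm. CTCAE v4.0 applies to all toxicity without a time limit, and 5.3.5 repeats that scale. Section 9.1 records events to the end of follow-up whether treatment-related or not, and judges serious events against the intervention. Section 10.2 counts all toxic effects observed. RTOG acute scoring is an additional instrument for the acute phase. Section 4.5 is an effectiveness schedule, so the absence of toxicity grading there is unsurprising, and 9.2 has its own follow-up checks.

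Most of this stands, and it rules out three stronger readings that a reader might infer:

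- **That late radiation harm lies outside the rules.** This needs the strict drug-coincidence reading, which the same paragraph contradicts at both ends of its window.
- **That SOXRT patients have no defined grading for about 92% of the horizon.** The 92% is time outside one instrument's window, not time without a scale and not a share of events lost.
- **That the safety comparison is shown to be biased towards SOXRT.** No late-toxicity rate is given. A strict drug-only definition would also drop late drug effects in both arms, and SOX receives six SOX cycles against four in SOXRT.

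The defence does not close the remaining gap. A grading scale is not an instruction to look, and 10.2 counts only what is observed. The protocol still does not name radiotherapy in the definition, relate the two scales, or say how radiotherapy-related events are assessed after 28 days.

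**Conclusion.** The point holds as a defect in how safety is defined and ascertained. Section 9.1 omits the randomised modality and contradicts its own window. Section 9.2 gives radiotherapy-specific assessment for about 6-8% of the 3-year horizon and leaves the rest to general rules without a clear schedule.

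Because only SOXRT is assigned radiation, under-capture of late radiation effects would tend to flatter that arm. That direction is inferred from the design, and its size cannot be estimated from the documents. The calendar figures assume no delays and a count from the start of induction; modest departures would not change the conclusion. The point does not touch the DFS or OS analysis. It merits an amendment because the remedy is cheap and uncollected data cannot be restored.

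**What to change.** - **9.1:** define an adverse event as one occurring during or after any study treatment, including radiotherapy, in line with the stated recording window. The serious-event definition then follows.
- **9.2:** keep RTOG acute scoring to 28 days after radiation, and state that CTCAE v4.0 governs radiotherapy-related events from then on. Say when the biweekly checks end and the 4.5 evaluations take over.
- **9.2 and 4.5:** require CTCAE grading in both arms at each 4.5 evaluation to the end of follow-up. Cover kidney, liver, small bowel and spinal cord, using the examination, biochemistry and imaging already scheduled.

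The cost is a short amendment, one CRF page and some site time. Toxicity figures for SOXRT may come out less favourable. No treatment, dose or stopping rule changes.

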# 10 Study assessment

10.1 Effective evaluation indicators: The primary purpose is: DFS. The secondary purpose is: and OS.

10.2 Safety evaluation index: including all toxic side effects and adverse events observed during the trial.

10.3 Sample content estimation: we hypothesised that synchronous radiotherapy would result in higher DFS. with a double significance level of 0.05 and a certainty of 80%. We expect that the 3-year DFS of SOX regimen combined with simultaneous radiotherapy can be at least 8% higher than that of the chemotherapy-only group, i.e., from 70% to 78%. Based on the sample size formula for the comparison of the two sample rates, the sample size needed for this project was calculated to be 516 patients; assuming that 20% of the patients would need to be excluded from the statistics, the total number of patients that would need to be enrolled in this project would be 620.

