| Randomization        | Patients were assigned in a 1:1 ratio to SOXRT arm or SOX arm by block randomization.                                                                                                                                                                                                                                                                                                                                                                                                                                                                                                                                                                                   |
| Treatment            | 
This is a multicenter, phase III clinical trial led by West China Hospital, Sichuan University. Patients will be randomly assigned to either the SOXRT arm (experimental group) or the SOX arm (control group).
 
SOXRT arm: Patients will receive one cycle of induction chemotherapy with the SOX regimen 21 days prior to radiotherapy initiation, followed by S-1-based concurrent chemoradiotherapy. After completing radiotherapy, patients will undergo three additional cycles of SOX chemotherapy, with the same dosing regimen as in the induction chemotherapy.
 
SOX arm: Patients will receive a total of six cycles of SOX chemotherapy.
 |
| Statistical Analysis | 
Categorical variables were compared with the use of Chi-squared test or Fisher' s exact test. Kaplan – Meier method was used to analyses the DFS and OS, log-rank test to assess the significance, and Cox proportional hazards model to calculate hazard ratio (HR). The median follow-up time was calculated by reverse-KM method. Statistical significance was defined as a two-side P value < 0.05.
                                                                                                                                                                                                                                                       |

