## 10.4 Statistical methods

All clinical data were analyzed using IBM SPSS Statistics (IBM Corp., Armonk, NY, USA. version 29.0) and R software (version 4.2.1). Categorical variables were compared with the use of Chi-squared test or Fisher's exact test. Kaplan–Meier method was used to analyses the DFS and OS, log-rank test to assess the significance, and Cox

proportional hazards model to calculate hazard ratio (HR). The median follow-up time was calculated by reverse-KM method. Statistical significance was defined as a two-side P value < 0.05.

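### The stated inputs (3-year DFS 70% vs 78%, two-sided 0.05, 80% power) need about 940 evaluable patients by the named two-rate formula, not 516; at 3 years, power is about 53% to 63% depending on how many are analysed

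*Protocol*

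**What the plan says.** Everything needed for the calculation is in the protocol.

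- **Effect:** section 10.3 expects 3-year DFS in the chemoradiotherapy arm to be "at least 8% higher than that of the chemotherapy-only group, i.e., from 70% to 78" per cent.
- **Error rates:** the same section works "with a double significance level of 0.05 and a certainty of 80" per cent. Section 10.4 confirms the sidedness: "Statistical significance was defined as a two-side P value < 0.05".
- **Formula:** "Based on the sample size formula for the comparison of the two sample rates".
- **Allocation:** the synopsis gives a 1:1 ratio.
- **Result:** "the sample size needed for this project was calculated to be 516 patients". Section 10.3 then raises this to 620 enrolled, "assuming that 20% of the patients would need to be excluded from the statistics".

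The synopsis also gives 620 as the number of patients in the trial, so 516 is a total over both arms (258 per arm). Section 4.5 calls the primary endpoint 3-year DFS but defines it as a time from randomisation to recurrence, metastasis or death. Section 10.4 analyses DFS by Kaplan-Meier, log-rank test and Cox model.

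**The concern.** A two-sample comparison of 70% with 78% is an 8-point difference between proportions that each carry sizeable variance. At two-sided 5% and 80% power it needs well over 400 patients per arm, so 258 per arm looks too small by nearly half.

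This calculation is the protocol's only justification for the size of a phase III trial. If it is wrong, the 80% power claim has no support. A non-significant result at 3 years would then be weaker evidence against an 8-point benefit than the protocol implies.

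**Working it through.** **Inputs** (sections 10.3 and 10.4, synopsis): p1 = 0.70, p2 = 0.78, difference 0.08, 1:1 allocation, z = 1.960 (two-sided 0.05) and 0.842 (80% power). The squared sum of the z-values is 7.849. The variances are 0.70 x 0.30 = 0.2100 and 0.78 x 0.22 = 0.1716, which sum to 0.3816.

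**Step 1. Reproduce 516.** Using the control arm's variance alone:

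7.849 x 0.2100 / 0.08² = 257.5, rounded up to 258; 2 x 258 = 516.

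This matches exactly, but a comparison of two rates needs both variances.

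**Step 2. Apply the named formula, per arm.**

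- Unpooled variance: 7.849 x 0.3816 / 0.0064 = 468.0, total 936.
- Pooled variance under the null (mean rate 0.74): [1.960 x √(2 x 0.74 x 0.26) + 0.842 x √0.3816]² / 0.0064 = 470.7, so 471 and total 942.
- Arcsine: total 940.
- Continuity-corrected: 495.4, so 496 and total 992.

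Other error rates do not rescue the figure. One-sided 0.05 with 80% power needs 738 to 742 in total. One-sided 0.05 with 90% power needs 514 per arm, which is close to 516, but the protocol states neither of those inputs and its 516 is a total.

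**Step 3. Power for 70% vs 78% at 3 years, two-sided 0.05.** With n per arm, the unpooled form is Φ(0.08√n / √0.3816 − 1.960). For n = 258 this is Φ(2.080 − 1.960) = 0.548; the pooled form gives 0.545.

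| Analysed (total) | Two-rate power | Log-rank, 3 years on every patient |
|---|---|---|
| 496 (620 x 0.8) | 52.8% to 53.2% | 129 events, 54% |
| 516 | 54.5% to 54.8% | 134 events, 55% |
| 620 | 62.2% to 62.6% | 161 events, 63% |

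The row for 496 is needed because 620 is 516 x 1.2 = 619.2 rounded up; removing 20% from 620 leaves 496, not 516.

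The log-rank column uses HR = ln 0.78 / ln 0.70 = 0.697, a mean 3-year event probability of (0.30 + 0.22)/2 = 0.26, and power Φ(√d x |ln HR| / 2 − 1.960) for d events, with |ln HR| = 0.3615.

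**Step 4. Difference detectable at 80% power.** Solving the two-rate formula for p2 gives 70% to 80.6% with 516 patients and 70% to 79.7% with 620.

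**Step 5. Events needed for 80% log-rank power.** By Schoenfeld's formula, 4 x 7.849 / 0.3615² = about 240. Under exponential DFS with these 3-year rates, and taking follow-up as equal for all patients, 240 events need about 4.9 years with 620 patients or about 6.3 years with 516.

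**The case against.** The strongest reply is that the planned analysis is a log-rank test, whose power depends on events rather than on rates at one time point. Section 4.5 defines DFS as a time to event, asks for evaluation at least every 6 to 12 months after treatment and gives no end to follow-up; no data cut-off is fixed. Assuming exponential DFS, proportional hazards and uniform accrual (the protocol gives neither accrual nor follow-up length), log-rank power would be:

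| Accrual + further follow-up (years) | 516 analysed | 620 analysed |
|---|---|---|
| 2 + 3 | 65% | 73% |
| 3 + 3 | 69% | 77% |
| 5 + 3 | 76% | 83% |
| 3 + 5 | 81% | 87% |

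This stands, and it limits the point. A reader might infer that the trial simply has 55% power, or that 80% is out of reach. The documents do not support either reading: 55% belongs to a 3-year comparison in 516 patients, and longer follow-up could reach 80%. Nor should the reader infer that the planned primary test compares 3-year rates; only the sample size calculation does so.

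The reply does not rescue section 10.3. The section names a two-rate formula and 3-year rates, and the protocol sets no event target, accrual period or analysis time that would secure the extra events. An unseen SAP might fix the analysis time, but it could not make 516 the result of the stated formula.

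A reader might also infer that 516 has no arithmetical origin. It has one (step 1), although a dropped variance term remains an inference about how the figure arose.

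**Conclusion.** The point holds as an arithmetic error in section 10.3. The stated 516 is about 55% of what the named formula requires (516/942 = 0.55), and no standard two-sided variant of that formula closes the gap. On the stated 3-year basis the 80% power is not delivered: if the assumed 8-point benefit is real, the chance of missing it is about 37% to 47%, depending on whether 620 or 496 patients are analysed.

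The sample size and 3-year two-rate power figures rest only on the protocol's own inputs. The event-based figures also assume proportional hazards, and those beyond 3 years assume exponential DFS. The 80% claim is therefore unsupported as written, not shown to be unattainable.

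**What to change.** Correct section 10.3 in one of two ways.

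1. **Keep the 3-year basis and state its power.** For 70% vs 78% at two-sided 0.05, give about 53% with 496 analysed, 55% with 516 and 62% to 63% with 620. Add the difference detectable at 80% power: 70% to 80.6% with 516, or 70% to 79.7% with 620. The cost is wording and a less favourable power statement.
2. **Keep 80% power without more patients.** State that the log-rank test already planned in section 10.4 will be run at about 240 DFS events (HR 0.697, proportional hazards). The cost is longer follow-up: about 4.9 years on average with 620 patients or 6.3 years with 516, under exponential DFS.

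In either case, remove the statement that the two-rate formula gives 516. If the size is instead to be recalculated for 80% power at 3 years, 942 evaluable patients with 20% excluded means 942/0.80 = 1,178 enrolled (rounded up), which is a different trial.

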## 5.3 Reduction and discontinuation of treatment

- 5.3.1 Patients can voluntarily withdraw from the study at any time.
- 5.3.2 In the event of a 3 or 4 grade haematological toxicity, the next cycle of chemotherapy needs to be given after the toxicity has returned to 0-1 grade and the dose of the next cycle of chemotherapy, S-1, is reduced by 25%.
- 5.3.3 In the event of  $\geq 2$  grade of non-haematological toxicity, chemotherapy should be delayed by 1 week. In the event of 4 grade toxicity during concurrent radiotherapy, other than alopecia, chemotherapy is discontinued and radiotherapy is continued whenever it is considered to be chemotherapy-related.
- 5.3.4 Discontinue radiotherapy only if radiotherapy-associated 3 grade skin inflammation occurs, until toxicity returns to 0-1 grade. If the patient's recovery period requires more than 3 weeks, treatment should be discontinued and the patient discharged from the group.
- 5.3.5 Toxicity was graded according to CTCAE 4.0 criteria.

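### Section 10.3 plans to leave 20% of patients out of the analysis, and the only mandated discharge can occur only in the SOXRT arm; unless discharged patients stay in follow-up and analysis, DFS and OS can be biased

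*Protocol*

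**What the plan says.** Section 10.3 derives the sample size in two steps. First, "the sample size needed for this project was calculated to be 516 patients". Then, "assuming that 20% of the patients would need to be excluded from the statistics", it concludes that "the total number of patients that would need to be enrolled in this project would be 620". It does not say who the 20% are, why they would be left out, or from which arm.

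Section 5.3.4 deals with grade 3 skin inflammation caused by radiotherapy. If recovery takes more than 3 weeks, "treatment should be discontinued and the patient discharged from the group". The control arm receives no radiotherapy, so the rule cannot apply there. The chemotherapy toxicity rules (5.3.2 and 5.3.3) delay, reduce or stop chemotherapy and discharge nobody. Voluntary withdrawal (5.3.1) is open to both arms.

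Section 4.5 measures DFS and OS from randomisation and asks for regular evaluation after treatment ends. Section 6, item 3, asks for observation during and after treatment. Section 10.4 analyses DFS and OS by Kaplan-Meier, log-rank test and Cox model, and contains no exclusion rule.

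**The concern.** Kaplan-Meier, log-rank and Cox methods do not need patients with incomplete follow-up to be removed. Such patients are censored and contribute up to their last assessment. Planning to leave one patient in five out of the statistics is therefore unnecessary, and it permits selection after randomisation.

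That matters more because the one discharge the protocol requires depends on treatment and can act in one arm only. A patient taken out of SOXRT for prolonged toxicity has no counterpart taken out of SOX. If discharge also meant leaving the DFS and OS analysis, the arms would no longer be the groups created by randomisation. The trial is open-label and its target is 8 percentage points in 3-year DFS, so a shift of a few points would be material.

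**Working it through.** **The plan's own figures.** Inputs from section 10.3: "with a double significance level of 0.05 and a certainty of 80" percent; 3-year DFS "i.e., from 70% to 78" percent; "Based on the sample size formula for the comparison of the two sample rates". The synopsis gives 1:1 allocation.

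- Per arm, n = [1.960·√(2·0.74·0.26) + 0.842·√(0.70·0.30 + 0.78·0.22)]² / 0.08² = 471, so 942 in total. The stated 516 is not reproduced. That is a separate matter and is not pursued here.
- 516 × 1.2 = 619.2, which gives the stated 620. Dividing instead, 516/0.80 = 645.
- Taken literally, excluding 20% of 620 removes 124 and leaves 496, which is 20 fewer than 516. The gap 620 − 516 = 104 is 16.8% of 620.

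**Direction of bias.** Assumptions, not in the documents: no true effect, 3-year DFS 70% in both arms, 310 per arm. A fraction f of SOXRT is deleted whose own 3-year DFS is q. The apparent SOXRT value is r = (0.70 − f·q)/(1 − f).

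- f = 5%, q = 40%: r = (0.70 − 0.020)/0.95 = 71.6%, a spurious gain of 1.6 points.
- f = 10%, q = 60%: r = (0.70 − 0.060)/0.90 = 71.1%, a gain of 1.1 points.
- f = 20%, q = 40%: r = (0.70 − 0.080)/0.80 = 77.5%, a gain of 7.5 points.
- Any f, q = 70%: r = 70%, no bias.
- f = 20%, q = 80%: r = (0.70 − 0.160)/0.80 = 67.5%, a loss of 2.5 points for SOXRT.

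The sign is therefore set by the prognosis of those removed, relative to the rest.

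**False-positive rate.** Simulation under no true effect: 310 per arm, exponential times, 3-year follow-up, log-rank test, rejection when z < −1.96 in favour of SOXRT (nominal 2.5%), 4000 trials per scenario. Twenty percent of patients are frail, with hazard k times the rest. The baseline hazard λ solves 0.8·exp(−3λ) + 0.2·exp(−3λk) = 0.70. Removed patients are all frail and all from SOXRT.

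| Share of SOXRT removed | Patients of 310 | k = 1.5 | k = 2 | k = 3 |
|---|---|---|---|---|
| 2% | about 6 | about 3% | about 3% | about 4% |
| 5% | about 16 | about 3% | about 4% | about 5% |
| 10% | 31 | 4% | 6% | 12% |
| 20% | 62 | 8% | 17% | 40% |

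Monte Carlo standard error near the nominal level is √(0.025·0.975/4000) = 0.25 points.

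The apparent gain in 3-year DFS is 2.2, 3.9 and 6.4 points in the 20% row. It is roughly 0.5 to 1.3 points in the 5% row and about 0.6 points or less in the 2% row. When the frail 20% are removed from both arms alike, the rate stays at the nominal level within simulation error.

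**The case against.** A reader might infer that the protocol removes 20% of patients, mainly from SOXRT, and so biases DFS and OS towards chemoradiotherapy. The documents do not support that, for these reasons.

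- **No link between the two sections.** The 20% is an enrolment allowance over all patients. Section 5.3.4 does not say that a discharged patient belongs to it or leaves the DFS and OS analysis. It sits under a heading about reducing and discontinuing treatment, so discharge may mean only coming off protocol treatment.
- **A narrow trigger.** It is grade 3 radiotherapy skin inflammation with slow recovery, not slow recovery from toxicity in general. Section 8.1 reports a low incidence of grade 3/4 toxicity with this regimen and names nausea and leukopenia as the most frequent. No rate for the trigger is given.
- **Follow-up is required.** Sections 4.5 and 6 call for it after treatment, and stopping treatment is not listed as an end to it.
- **Prognosis is unstated.** Nothing in the protocol ties a skin reaction to DFS.
- **An analysis plan may exist.** An analysis set may be defined there, so its absence from the protocol is not a fault in itself.

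All five stand and limit the size of the point. They do not remove it. The 20% is expressly described as left out of the statistics, whichever patients are meant. Section 5.3.4 already stops treatment in the same sentence, so discharge from the group reads naturally as something further. Sections 4.5 and 6 do not settle what happens to a patient so discharged.

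**Conclusion.** The point holds in conditional form. The wording of 10.3 and 5.3.4 together allows exclusions after randomisation that depend on treatment and can fall on one arm. Whether they would bias DFS and OS, and in which direction, depends on three things the documents do not give: whether discharged patients are dropped, how many there are, and their prognosis.

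The trigger is narrow, so the 2–5% rows are the more relevant ones for discharge alone. There the false-positive rate favouring SOXRT is about 3–5% against 2.5%, and only if the removed patients fare worse. The 8–40% range is the worst case considered: 62 SOXRT patients deleted, all frail, and none from SOX. It shows what the planned 20% could do if it fell on one arm, not what the protocol predicts. All rates assume complete deletion of the removed patients.

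**What to change.** - **Sections 10.3 and 10.4:** state that the primary DFS and OS analyses include every randomised patient in the assigned arm. Replace the phrase about exclusion from the statistics with an allowance for loss to follow-up, handled by censoring.
- **Section 5.3.4:** clarify that discharge does not end DFS and OS follow-up and does not remove the patient from the analysis. The clinical discontinuation rule itself is left as it is.
- **Analyses with exclusions:** label any of these as sensitivity analyses.

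The cost is a few sentences and continued follow-up of discharged patients, including those already enrolled. Outcome data not collected after discharge may be hard to recover later, which favours an early change. Keeping patients who stopped treatment may dilute the effect estimate somewhat; that is the price of keeping the randomised comparison intact.
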